---

# 1. Background

Acute exacerbations of chronic obstructive pulmonary disease (COPD) result in over 9,000 hospital admissions every year in New Zealand (NZ). Nebulised medication is routinely administered to patients with an acute exacerbation and can be delivered via either high flow oxygen or air.

Oxygen driven nebulisers expose patients to high concentrations of inspired oxygen. The risks of high concentration oxygen have been shown by the recent randomised controlled trial (RCT) in which high concentration oxygen therapy (supplementary oxygen 8-10 L/min and high flow oxygen-driven nebulisers for bronchodilator delivery) caused a 2.4-fold increased risk of death compared with titrated oxygen therapy (supplementary oxygen titrated as needed to achieve an oxygen saturation of 88-92% and air-driven nebulisers for bronchodilator delivery) in the management of severe exacerbations of COPD. Hypercapnia, an elevated arterial carbon dioxide tension ( $\text{PaCO}_2$ ), is a known risk of high concentration oxygen therapy in patients with COPD, and oxygen driven nebuliser use has been associated with marked increases in  $\text{PaCO}_2$ , which resulted in stupor, seizures and death.

The British Thoracic Society (BTS) recommends titrated oxygen therapy to achieve oxygen saturations of 88-92% and air-driven nebuliser use for acute exacerbations of COPD. It is recommended that if air-driven nebulisers are unavailable, use of oxygen driven nebulisers should be limited for up to six minutes. However, it is likely that in clinical practice patients have oxygen delivered through nebulisers for longer than this, particularly if two nebulisers are being given sequentially. We have shown that air-driven nebulisers will prevent the increase in  $\text{PaCO}_2$  that results from use of oxygen-driven nebulisers in patients with stable COPD. However, there are only two published RCTs in patients with acute exacerbations of COPD. While acknowledging the important limitations of these studies, including lack of blinding, administration of single bronchodilator doses and low power, they did identify increased risk of an elevation in  $\text{PaCO}_2$  in COPD patients with hypercapnia.

The risks of oxygen delivered nebulisation in acute exacerbations of COPD need to be robustly defined to identify whether the widespread implementation of air driven

nebulisers is required to ensure the safe delivery of bronchodilators by nebulisation to this at-risk patient group.

---

## **2.Design & Objectives**

### **A. DESIGN**

A parallel group double blinded RCT comparing the effect of air versus oxygen driven bronchodilator nebulisation on PaCO2, pH and oxygen saturation (SpO2) in patients admitted to hospital with an acute exacerbation of COPD. Ninety patients will be recruited and randomised to receive two 15 minute administrations of salbutamol by nebulisation, delivered by air or oxygen at a flow rate of 8L/min.

### **B. OBJECTIVES**

- i. To compare the effects of air versus oxygen driven bronchodilator nebulisation on pCO2, pH and SpO2 in acute exacerbations of COPD
- ii. To determine if the BTS recommendation of six minute oxygen driven nebuliser use avoids the risk of an oxygen induced increase in pCO2

### **C. HYPOTHESES**

- i. Oxygen driven bronchodilator nebulisation results in increased pCO2 in exacerbations of COPD compared with air driven bronchodilator nebulisation
- ii. Oxygen driven bronchodilator nebulisation results in a reduction in pH in exacerbations of COPD compared with air-driven bronchodilator nebulisation
- iii. The increase in pCO2 and reduction in pH secondary to oxygen-driven nebuliser use are clinically significant in some patients, defined as  $\geq 8$ mmHg change in PaCO2 or  $\geq 0.06$  change in pH.
- iv. Clinically significant elevations in pCO2 secondary to oxygen-driven nebuliser use occurs within six minutes of commencement of nebulisation in some patients
- v. Cessation of oxygen-driven bronchodilator nebulisation may result in rebound hypoxaemia

---

## 3. Study Subjects

### A. INCLUSION CRITERIA

- i. Ninety patients admitted to Hutt Valley or Wellington Regional Hospital medical inpatient wards with a primary admission diagnosis of an exacerbation of COPD.
- ii. Participants must have the mental capacity to allow them to provide written informed consent.

### B. EXCLUSION CRITERIA

- i. Age <40 years at time of randomisation
- ii. Requirement for assisted non-invasive ventilation at time of randomisation
- iii. Baseline  $PtCO_2$  >60mmHg at time of randomisation
- iv. Requirement for  $\geq 4$ L/min of oxygen via nasal cannulae to maintain  $SpO_2$  between 88-92% prior to or during titration
- v. Any other condition which, at the investigator's discretion, is believed may present a safety risk or impact the feasibility of the study or the study results.

---

## 4. Randomisation and blinding

### A. RANDOMISATION

Randomisation will be 1:1 via a block randomised (block size 6) computer generated sequence, provided by the study statistician independent of recruitment and assessment of participants. The allocated intervention will be stored in an opaque sealed envelope and opened at the time of randomisation by the un-blinded investigator.

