## **iv. Roles of the un-blinded investigator**

- a. Recording medical history, demographics and obtaining written informed consent (either investigator can do this prior to blinding).
- b. CBG sampling
- c. Randomisation
- d. Administration of the randomised intervention
- e. Recording and monitoring of finger probe SpO2
- f. Increase oxygen therapy if SpO2 <85%.

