### **ii. Intervention**

For at least 15 minutes the un-blinded investigator will titrate oxygen therapy via nasal cannulae to achieve an SpO2 of 88-92%. Note this may mean the participant breathes room air. If the participant requires  $\geq 4\text{L/min}$  via nasal cannulae, they will be excluded.

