## **10. Power and Statistical Methods**

A difference in  $PaCO_2$  of 4 mmHg represents a physiologically significant change.  
 In our controlled study of oxygen versus air driven nebulisers in stable COPD the standard deviation of  $P_tCO_2$  was 5.5. With 90% power and alpha of 5% this requires a total of 82 patients to detect a 4 mmHg difference. We anticipate a drop-out rate of <10% so our target recruitment is 90 patients. Analysis will be by intention to treat. Participants recruited will be stratified in to groups that were receiving oxygen immediately prior to randomisation or those that were not. Our primary analysis is ANCOVA with  $P_tCO_2$  as the response variable, and randomised treatment and baseline  $P_tCO_2$  as co-variables. For other continuous outcome variables we will also use similar ANCOVA. Exploratory analyses for  $P_tCO_2$ , heart rate and  $SpO_2$  taken at five minute intervals will be presented graphically and analysed by mixed linear models.

---

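### A fixed block size of 6, stated in the protocol, lets an un-blinded investigator who tracks earlier allocations foresee up to an expected quarter of later ones before the envelope is opened

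*Protocol*

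**What the plan says.** Section 4.A fixes the ratio and one block size: "Randomisation will be 1:1 via a block randomised (block size 6) computer generated sequence". The sequence is "provided by the study statistician independent of recruitment and assessment of participants". Each allocation is kept in an opaque sealed envelope, "opened at the time of randomisation by the un-blinded investigator". The section does not vary or withhold the block size, and it does not say that the envelopes are numbered.

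Section 4.B.iv lists the tasks of the un-blinded investigator. Besides randomisation and giving the intervention, they include "Recording medical history, demographics and obtaining written informed consent (either investigator can do this prior to blinding".

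Section 6.D.ii gives the same role the wash-in: "For at least 15 minutes the un-blinded investigator will titrate oxygen therapy via nasal cannulae". A patient who reaches the oxygen-flow limit there is excluded. Section 6.E then takes the baseline measurements, and the envelope is opened after them.

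Section 3.B criterion v adds a discretionary exclusion: "Any other condition which, at the investigator's discretion, is believed may present a safety risk". It covers conditions thought to affect the study results and does not say which investigator decides. Section 6.A lets patients be recruited at any point in the admission.

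Section 10 says: "Participants recruited will be stratified in to groups that were receiving oxygen immediately prior to randomisation or those that were not". Section 4.A does not mention strata, so the number of lists is unclear.

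**The concern.** Concealment has to hold up to the moment a patient is irrevocably in the trial. Here the role that learns each past allocation also takes part in the steps before the next one. Once three places of one arm in a block of six are used, the rest of that block is known.

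Someone with that knowledge could, without intending harm, delay a visit or judge a borderline patient unsuitable according to the arm that comes next. Section 6.B has the history recorded before randomisation, including earlier hypercapnic failure, earlier assisted ventilation and home oxygen. The recruiter can therefore form a view on who is likely to retain CO2.

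The primary model in section 10 contains treatment and baseline PtCO2 only. Adjustment for baseline limits imbalance in the starting value. It need not remove selection on history that predicts the response to oxygen beyond that value. The blinded recording of PtCO2 protects the measurement, not the choice of who enters and when.

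**Working it through.** The protocol gives no figure for predictability, so there is none to reproduce. The stated sample size is not affected.

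**Inputs.** Ratio 1:1 and block size 6 (section 4.A); 90 patients (sections 2.A and 10); two hospitals (section 3.A). The share of earlier allocations known to the recruiter, q, is not in the protocol and is varied below.

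**1. Certain allocations, full tracking (q = 1).** A 3+3 block has C(6,3) = 20 equally likely orders. An allocation is certain once the other arm's three places are used.
- 1 certain: probability 0.6
- 2 certain: probability 0.3
- 3 certain: probability 0.1

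Mean = 1 × 0.6 + 2 × 0.3 + 3 × 0.1 = 1.5 of 6 = 25%.

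One list of 90 has 90/6 = 15 blocks, so 15 × 1.5 = 22.5 allocations are expected to be certain. The variance per block is (0.6 + 4 × 0.3 + 9 × 0.1) − 1.5² = 0.45. The SD over 15 blocks is √(15 × 0.45) = 2.6, which puts the share at about 19% to 31% (±1.96 SD).

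**2. Best guess, full tracking.** The rule is to guess the arm with fewer patients so far and toss a coin when they are level. With n = 3 per arm, expected correct guesses per block = n + (4ⁿ/C(2n,n) − 1)/2 = 3 + (64/20 − 1)/2 = 4.1. That is 4.1/6 = 68.3%, against 50% by chance.

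**3. Several lists.** If section 10 means separate lists, some last blocks are incomplete. Simulation with 90 patients spread evenly gives about 24% certain for two lists and 23% for four.

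**4. Incomplete tracking.** Suppose each earlier allocation is known with probability q and block boundaries are known. Certainty then needs all three allocations of the used-up arm to be known, so the share is 0.25 × q³.

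| q | Formula | Simulation |
|---|---|---|
| 1 | 25% | 24.9% |
| 0.75 | 0.25 × 0.422 = 10.5% | 10.4% |
| 0.5 | 0.25 × 0.125 = 3.1% | 3.2% |

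**5. Effect of varying the block size.** This was simulated for 90 patients with full tracking, and with the recruiter knowing which sizes are in use but not their order.

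| Block sizes | Certain allocations |
|---|---|
| Fixed 6 | about 25% |
| Random 4/6 | about 5% |
| Random 2/4/6 | about 4% |
| Random 4/6/8 | about 2% |

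The guessing rule in step 2 does not use the block size, so varying the size hardly changes its success. By the same formula, blocks of 4, 6 and 8 give 2.83, 4.1 and 5.33 correct guesses. Equally likely sizes give (2.83 + 4.1 + 5.33)/18 = 68.1%. The gain is in certainty, not in above-chance guessing.

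**The case against.** A fixed block with an independent statistician and opaque sealed envelopes is a weaker choice, not an error or a contradiction. The routes to bias are also limited. Titration aims at a set saturation range with a numerical exclusion limit. From the end of set-up the transcutaneous monitor is behind the screen with the blinded investigator, so the person opening envelopes is not the one reading wash-in PtCO2. The primary outcome is an instrument reading taken blind and adjusted for baseline. All of this stands and narrows the risk. It does not close it, because history and recruitment timing remain available to the un-blinded role.

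A reader might infer four stronger things that the protocol does not support:
- **That a quarter of allocations are in fact known.** The protocol defines a role, at two hospitals, and does not say how many people fill it or whether they share past allocations. The 25% is the full-tracking case.
- **That the block size is public knowledge.** The text shows only that it is stated in the protocol that investigators work from.
- **That the un-blinded investigator controls criterion v.** The criterion does not name which investigator. Nothing withholds it from that role either.
- **That the t=0 oxygen flow could be set after the allocation is seen.** Sections 6.E.i and 6.E.ii already have it recorded before the envelope is opened.

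No bias in mmHg or in type I error has been shown, and the protocol gives no inputs from which to estimate one.

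**Conclusion.** The point holds as a conditional weakness in allocation concealment. With one fixed and known block size, and an un-blinded role that also acts before randomisation, the expected share of allocations certain in advance depends on tracking. It is about 25% (about 22 of 90) with full knowledge of one list and 23–24% with two to four lists. It is about 10% if three quarters of earlier allocations are known, and about 3% if half are. Best-guess accuracy under full tracking is 68%. These figures assume that the recruiter knows the block size and where blocks begin. They measure the opportunity for selection and say nothing about whether selection took place. Baseline PtCO2 adjustment limits the consequence but need not remove selection on history. The change is worth making because it is cheap and takes away most of the certainty.

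**What to change.** - Have the independent statistician generate the list with randomly varying block sizes (for example 4, 6 and 8). If recruitment has started, do this for the unused envelopes.
- Remove the block size from section 4.A. Say only that allocation is 1:1 in permuted blocks of varying size, with the sizes held by the statistician and not disclosed to site staff.
- Require sequentially numbered envelopes, opened in order.
- Require any criterion v exclusion to be documented, with its reason, before the envelope is opened. This does not prevent an exclusion made with foreknowledge, but it leaves a record that can be checked.

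The cost is one regenerated list and a short edit. Arm sizes may differ slightly at the end. With a largest block of 8 the difference cannot exceed 4 per list, against at most 3 for an incomplete block of 6. As step 5 of the working shows, above-chance guessing remains, so the change reduces the weakness and does not abolish it.

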### B. BLINDING

#### i. Blinding of the blinded investigator during the study visit

The blinded investigator will be sat behind a portable screen so that they cannot see the participant or pulse oximeter screen. The participant will be asked not to

comment out loud whether they are wearing their mask or nasal prongs. The SpO2 on the transcutaneous monitor will be covered.

## **ii. Blinding of the laboratory technician**

The laboratory technician analysing the Capillary Blood Gas (CBG) sample will be masked to the randomised treatment.

## **iii. Blinding of the participant**

The oxygen and air cylinders will not be distinguishable from each other to maintain blinding of the participant as to which gas their nebuliser is driven by. Participants will not be advised which treatment regimen they are randomised to or of the detail that one regimen involves removal of nasal prongs, if worn, (oxygen-driven) and the other does not (air driven). They will be informed, however, that their oxygen saturations will be monitored closely and if there are any concerns the regarding low oxygen saturation the un-blinded investigator will provide appropriate oxygen therapy immediately. Participants will not be able to see the screen of the pulse oximeter.

## **iv. Roles of the un-blinded investigator**

- a. Recording medical history, demographics and obtaining written informed consent (either investigator can do this prior to blinding).
- b. CBG sampling
- c. Randomisation
- d. Administration of the randomised intervention
- e. Recording and monitoring of finger probe SpO2
- f. Increase oxygen therapy if SpO2 <85%.

## **v. Roles of the blinded investigator**

- a. Recording medical history, demographics and obtaining written informed consent (either investigator can do this prior to blinding).
- b. Recording of PtCO2
- c. Recording of heart rate
- d. Advise the cessation of the intervention should the PtCO2 rise by  $\geq 10$ mmHg from baseline.

---

## 5. Nebuliser equipment

- a. Hudson RCI Micro Mist Nebuliser Masks (Hudson RCI, Durham, North Carolina, USA) will be used to deliver the air and oxygen driven nebulised bronchodilator.
- b. Salbutamol 2.5 mg will be used for each 15 minute nebulisation
- c. Oxygen and air to drive the nebulisation will be supplied in compressed portable cylinders (size D).

---

## 6. Study visit conduct

### A. RECRUITMENT, TIMING AND CONSENT

Potentially eligible participants will be identified on the wards and invited to take part in the study. Patients can be recruited at any time during their medical admission; however the study visit should be timed to deliver the nebuliser regimen as close as possible to the time of the next prescribed bronchodilator dose. Written Informed consent will take place prior to any study specific procedures.

### B. DEMOGRAPHIC DATA COLLECTION

#### i. The following will be collected on medical history

- a. Primary reason for admission
- b. Age and ethnicity
- c. Pack year history
- d. History of:
  - a. Long term oral prednisone use
  - b. Home oxygen use
  - c. Home nebuliser use
  - d. Previous hypercapnic respiratory failure
  - e. Previous assisted ventilation
- e. Medical comorbidities
- f. Medication history
- g. Current oxygen prescription (if any)

- h. Date, time, dose and method (nebuliser, spacer or inhaler only) of last bronchodilator medication(s)
- i. Date, time, dose and method (nebuliser, spacer or inhaler only) of the next prescribed bronchodilator medication(s)

**ii. The following will be measured**

- a. Weight and height

NOTE: Should the participant be too unwell to take these measures, data may be collected from clinical records or patient history. The method of collecting this data (investigator measurement, clinical records or patient history must be documented).

- b. In participants that are able to perform spirometry, this will be done using a using a Micro Spirometer (Micro Medical Ltd, Rochester, UK) to measure FEV1 and FVC, and according to ATS/ ERS criteria.

## **C. STUDY SET UP**

**i. Transcutaneous monitor calibration**

The transcutaneous monitor screen displaying StO2 is to be covered. The transcutaneous monitor will be attached to the participant's earlobe as per manufacturer's instructions. If the reading from the earlobe is inadequate, the forehead (over frontal bone) or clavicle can be used as back-up sites, as per the manufacturer's recommendations. A calibration period of at least 20 minutes will take place. This will be followed by measurements of PtCO2 every 1 minute until consecutive measurements are within 1mmHg.

**ii. Pulse oximeter application**

The finger oximeter will then be placed on the participant's index finger. The StO2 screen will be uncovered on the transcutaneous monitor and the un-blinded investigator will record the time, StO2 and SpO2. The transcutaneous monitor screen displaying StO2 will be covered again and until t=80.

### **iii. Blinded investigator set up**

From this point on and until t=80 minutes the blinded investigator and transcutaneous monitor will go behind a screen to avoid visualisation of the participant and pulse oximeter screen.

## **D. WASH IN PERIOD**

### **i. Baseline measures**

- a. The un-blinded investigator will record the time, SpO2 and nasal cannulae oxygen therapy flow (if any)
- b. The blinded investigator will record the time, PtCO2 and heart rate

### **ii. Intervention**

For at least 15 minutes the un-blinded investigator will titrate oxygen therapy via nasal cannulae to achieve an SpO2 of 88-92%. Note this may mean the participant breathes room air. If the participant requires  $\geq 4\text{L/min}$  via nasal cannulae, they will be excluded.

### **iii. Monitoring and measurements by the un-blinded investigator**

- a. Every 5 minutes (to the nearest minute) record the time and SpO2.
- b. Monitor the SpO2 and if the nasal cannulae oxygen flow is changed, document the time and new oxygen flow

### **iv. Monitoring and measurements by the blinded investigator**

- a. Every 5 minutes (to the nearest minute) record the time, PtCO2 and heart rate.

## **E. RANDOMISED REGIMEN**

### **i. Baseline measures**

- a. At the end of the wash in and immediately prior to the randomised regimen the un-blinded investigator will take a CBG, as per the SOP. On visualisation of blood entering the capillary tube they will ask the blinded investigator to record the time and PtCO2.

- b. Immediately after the CBG sampling, the following baseline (t=0 min) measurements will be made:
  - i. The un-blinded investigator will record the time, SpO2 and nasal cannulae oxygen therapy flow (if any).
  - ii. The blinded investigator will record the time, PtCO2 and heart rate

## **ii. Randomisation**

The randomisation envelope will be opened by the un-blinded investigator and regimens applied as below.

## **iii. Regimens**

### Air driven nebuliser regimen

- a. t=0-15 min: 2.5 mg salbutamol by nebulisation, delivered by air at a flow rate of 8L/min
- b. t=15-20 min: Removal of nebuliser mask
- c. t=20-35 min: 2.5 mg salbutamol by nebulisation, delivered by air at a flow rate of 8L/min.

The nebuliser is to continue running for the entire 15 minutes at t=0-15 min and t=20-35 min, even if the bronchodilator medication has dissipated.

Oxygen therapy is to be continued to be titrated by the un-blinded investigator using nasal cannulae (worn under the nebuliser mask at 0-15 and 20-35 min). Note that if the patient was not receiving oxygen before the intervention (was breathing room air) this will continue unless the oxygen saturations drop to <85%. If this occurs the nebuliser mask will be removed, nasal prongs attached and oxygen given before reattaching the nebuliser mask. If this does happen it will be recorded in the case report form.

### Oxygen driven nebuliser regimen

- a. t=0-15 min: 2.5 mg salbutamol by nebulisation, delivered by oxygen at a flow rate of 8L/min
- b. t=15-20 min: Removal of nebuliser mask

- c. t=20-35 min: 2.5 mg salbutamol by nebulisation, delivered by oxygen at a flow rate of 8L/min.

The nebuliser is to continue running for the entire 15 minutes at t=0-15 min and t=20-35 min, even if the bronchodilator medication has dissipated.

Any nasal cannulae oxygen therapy is to be discontinued and nasal prongs removed, during t=0-15 min and t=20-35 min. Oxygen must be restarted at the same flow given prior to nebuliser delivery (i.e. at t=15 the oxygen must be started at the flow delivered at t=0, and at t=35 it must be started again at the flow delivered at t=20 minutes). Note that if the patient was not receiving oxygen before the intervention (was breathing room air) this will continue unless the oxygen saturations drop to <85%. If this occurs the nebuliser mask will be removed, nasal prongs attached and oxygen given. If this does happen it will be recorded in the case report form.

